## Abstract

**Background:**

Coronary heart disease (CHD) is typically associated with many cardiovascular risk factors (e.g., elevated blood pressure), low health-related quality of life, depression, anxiety and psychological stress. Expressive writing (EW) has shown beneficial effects on such variables in both people from the community and in patients with a variety of chronic illnesses. However, no study to date has evaluated the physical and psychological effects of the expressive writing procedure on coronary patients referred to cardiac rehabilitation (CR).

**Methods:**

The clinical effectiveness of a 2-week disease-related expressive writing procedure (writing about one's deepest thoughts and feelings regarding the experience with heart disease) compared with the standard writing task (writing about one's deepest thoughts and feelings about the most traumatic or negative event experienced in the life), a neutral writing condition (writing about the facts regarding heart disease and its treatment) and an empty control condition will be evaluated in a randomized controlled clinical trial (RCT) with repeated follow-up measurements at 3, 6 and 12 months after discharge from CR. The primary outcome is health-related quality of life (SF-12). Secondary outcome measures are depression (BDI-II), anxiety (BAI) and post-traumatic growth (PTGI). Furthermore, the study will explore the moderating effects of coping styles, type D personality, perceived emotional support and participants' evaluative ratings of the writing interventions on the main experimental effects in order to identify sub-groups of patients showing different results.

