## Methods

### Study design

A four-arm randomized controlled clinical trial with four follow-up assessments (immediately before discharge from hospital, 3 months, 6 months and 12 months after discharge) will be carried out in order to test the following primary hypotheses/outcomes: 1) a modified disease-related expressive writing intervention is effective in enhancing physical and psychological health outcomes (HRQoL, anxiety and depression symptoms, medical visits for CVD-related morbidities) relative to a sham condition in which patients write solely about the facts of their experience with CVD and relative to a control empty condition; 2) the modified disease-related expressive writing intervention is more effective in enhancing physical and psychological health outcomes than a standard expressive writing condition in which patients write about the their deepest thoughts and feelings about the most traumatic or negative event they have experienced in their life. Further hypotheses/outcomes concern post-traumatic growth and are: 1) the modified disease-related expressive writing intervention is effective in enhancing post-traumatic growth relative to sham and control conditions; 2) the modified disease-related expressive writing intervention is more effective in enhancing post-traumatic growth than the standard expressive writing task.

Secondary analyses will be conducted in order to explore the relative efficacy of the writing conditions as a function of patients' gender, age, coping styles, negative affectivity and social constraint (type D personality factors), perceived social support and evaluative ratings of the writing intervention. Accordingly, significant interactions between the experimental conditions and the moderator variables mentioned above are postulated such that, for example, patients low on avoidance will benefit more from expressive writing than avoidant patients and that patients perceiving low social support will benefit more than patients perceiving high social support.

The Medical Ethics Committee of Istituto Auxologico Italiano approved the study protocol.

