### Outcome Measures

#### SF-12

The SF-12 Health Survey is a measure of physical and mental health. It is the short form of the most popular SF-36 and consists of the 12 items that were found to be the best predictors of the two SF-36 physical and mental summary scores (referred to as PCS-36 and MCS-36, respectively) in the US validation study [39]. Selected items and weights derived from the general US population were then used to score the physical and mental summary scores (referred to as PCS-12 and MCS-12, respectively). The PCS-12 and MCS-12 were very highly correlated with PCS-36 and MCS-36 (r = 0.951 and 0.969, respectively) and were very weakly correlated (r = 0.06) with each other in the US sample. In the present study, the Italian version of the SF-12 will be used [40] and the two summary scores (PSC-12 and MCS-12) will be computed with weights derived from the Italian validation sample.

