### Statistical analysis

Data entry will be conducted by a trained research assistant who will be aware of participants' condition assignment but not of the research hypotheses. Preliminary analyses will be performed to examine assumptions for parametric statistical analysis and baseline equivalence among groups. Given the longitudinal nature of the data (repeated measurements), multilevel modeling analysis in MLwiN 2.21 (Centre for Multilevel Modeling-CMM, University of Bristol) will be used to study health outcomes (physical and mental health, anxiety, depression, post-traumatic growth and number of medical visits for cardiovascular morbidity) as functions of time and experimental conditions. This will allow testing of experimental hypothesis as cross-level interactions between slopes representing time (1^th ^level) coded as 0 for the first (immediately before discharge from hospital) follow-up, as 1 for the second (3-month) follow-up, as 2 for the third (6-month) follow-up and as 3 for the fourth (12-month) follow-up, and a categorical covariate representing conditions (2^nd ^level). We will start with a simple random intercept model (for calculating intra-class correlation [ICC]) and a simple linear growth model, followed by a model with experimental conditions as a time-invariant covariate. We then will structure more complicated models, including models with different within-individual covariance structures and models with nonlinear growth patterns. A critical alpha of 0.05 will be considered for hypothesis testing. Furthermore, on the basis of the best multilevel models structured in the primary analyses, we will explore the moderating effects of some putative covariates at level 2 such as gender, age, coping styles, negative affectivity and social inhibition (Type D personality dimensions), perceived social support and writings ratings. For these secondary explorative analyses no level of significance will be defined. Readers interested in further discussion of analyzing longitudinal data with multilevel modeling analysis are referred to an excellent guide by Kwok et al. [48] as well as a thorough treatment of the issue by Singer and Willett [49].

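### The abstract makes SF-12 the only primary outcome, the design section makes four outcomes primary, and neither says which SF-12 score counts or how error is shared over the contrasts

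*Protocol article*

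**What the plan says.** - **Abstract, Methods.** "The primary outcome is health-related quality of life (SF-12). Secondary outcome measures are depression (BDI-II), anxiety (BAI) and post-traumatic growth (PTGI"). Medical visits are in neither list.
- **Study design.** The trial is run "in order to test the following primary hypotheses/outcomes". The outcomes under that label are "HRQoL, anxiety and depression symptoms, medical visits for CVD-related morbidities". The first hypothesis sets disease-related expressive writing (DS-EW) "relative to a sham condition in which patients write solely about the facts of their experience with CVD and relative to a control empty condition". The second sets it against standard expressive writing (S-EW). Post-traumatic growth comes afterwards, as a further hypothesis.
- **Outcome Measures, SF-12.** "the two summary scores (PSC-12 and MCS-12) will be computed", one physical and one mental. Their correlation in the US validation sample is given as 0.06.
- **Sample size calculation.** The trial is sized on health-related quality of life alone, with f = 0.4, two-sided alpha 0.05, power 0.82, 20% dropout and 92 patients (23 per arm). The section calls the study partly exploratory.
- **Statistical analysis.** All outcomes go into the same kind of multilevel model, tested as a time-by-condition interaction with condition categorical. "A critical alpha of 0.05 will be considered for hypothesis testing". No significance level is set for the moderator analyses.

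**The concern.** Depression and anxiety cannot be both secondary and part of the primary hypotheses, and medical visits move from unlisted to primary. Since Study design holds growth apart as a further hypothesis, it does rank the outcomes, and its ranking differs from the abstract's.

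The abstract's version is not a single endpoint either. SF-12 gives two scores that were almost uncorrelated in the US sample, and the article does not say whether the physical score, the mental score, either or both must show an effect.

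The primary hypotheses therefore cover between 2 × 3 = 6 score-by-contrast comparisons (SF-12 only) and 5 × 3 = 15 (all listed outcomes), with one flat alpha. A positive result on any listed outcome could be reported as primary with support from one section or the other. Medical visits deserve particular care, because they are self-recorded and are coded by an investigator who knows the allocation.

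**Working it through.** **1. The plan's own figure.** One-way analysis of variance, four groups, f = 0.4, alpha 0.05. The noncentrality is f² × N. With 19 per arm, N = 76, this is 0.16 × 76 = 12.16 and power is 0.823. Adding 20% gives 76 × 1.2 = 91.2, so 92, which matches both the size and the power of 0.82. Alternatively, 18 per arm (power 0.799) divided by 0.8 is 22.5, so 23 per arm, again 92. The sample size reproduces as **one four-group comparison on one outcome**. Neither several outcomes nor pairwise contrasts enter it.

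**2. Inputs for the error rate.**
- Completers: 92 × 0.8 = 73.6, about 18 per arm.
- Contrasts: DS-EW against sham, empty control and S-EW (Study design).
- Scores: physical and mental SF-12, anxiety, depression and visits, five in all.
- Alpha: 0.05 (Statistical analysis).
- Correlation between outcomes: not given for this population. **Assumption:** 0 to 0.7, equal for all pairs.

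**3. Simple reference.** If all tests were independent, the chance of at least one false positive is 1 − 0.95^m. For m = 6 it is 0.265, and for m = 15 it is 0.537. The three contrasts share the DS-EW arm and so correlate at 0.5, which lowers these values. Simulation is therefore needed.

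**4. Simulation under no true effect in any arm.** Normal outcomes, 18 per arm, pooled variance, one comparison per outcome and contrast. The article does not fix the form of the test, so three readings were run:

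| Reading | Physical and mental SF-12 | Five scores |
|---|---|---|
| Three contrasts, each two-sided at 0.05 | 20–23% | 34–49% |
| One omnibus four-group test per score | 8–10% | 16–23% |
| Benefit only; hypothesis 1 needs both contrasts, hypothesis 2 separate | 5–6% | 8–13% |

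The lower end of each range belongs to correlation 0.7 and the upper end to correlation 0. If quality of life is counted as one score (four outcomes), the first two rows become about 30–42% and 14–19%. With a single SF-12 score they are about 12.5% and 5%.

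**5. Power cost of adjustment.** Assumption: d = 0.8, the two-group equivalent of f = 0.4. The noncentrality is d × √(n/2), which is 0.8 × √9 = 2.4 for n = 18. With variance pooled over the four arms and 18–19 per arm, pairwise power is 66–68% at 0.05 and 55–57% at 0.025.

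**The case against.** Several points against the concern have weight.

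- **Form of test.** Pairwise tests are inferred from the hypotheses. The Statistical analysis section describes only a time-by-condition interaction, and the sample size is for an omnibus comparison. This stands, and is why the omnibus reading is shown beside the pairwise one.
- **Direction and conjunction.** The hypotheses speak of benefit, and the first can be read as requiring superiority to both sham and empty control. This also stands. On that reading SF-12 alone stays near 5%, and the excess comes from the added outcomes.
- **Model.** The simulation uses one normal comparison per outcome, whereas the plan fits growth models and visits are counts. The figures are therefore approximate. The number of tests and their correlation drive the result, and those do not depend on the model.
- **Condensed article.** An adjustment method may sit in an analysis plan that is not shown. That is fair for the method, and the word unadjusted would be an inference from silence. It does not excuse two published sections that name different primary outcomes.
- **Partly exploratory.** The article uses this phrase to justify assuming a large effect. It still states primary hypotheses and a critical alpha, and withholds a significance level only from the moderator analyses.

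A reader might go further and infer that a false primary claim is more likely than not. The documents do not support that. The five listed scores stay below one half once the shared arm is allowed for. Higher figures need post-traumatic growth added, and neither section calls growth primary.

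**Conclusion.** The contradiction is in the text and needs no assumption: the abstract and the Study design section disagree on what is primary, and the choice between the two SF-12 scores is open. Its size depends on how the tests are read. On the design section's list the familywise error is about 34–49% (three two-sided contrasts), 16–23% (omnibus) or 8–13% (benefit only, conjunctive), so it exceeds 5% on all three readings. Keeping to SF-12 brings this to about 20–23%, 8–10% and 5–6%. These figures assume no true effect, about 18 completers per arm and outcome correlations of 0 to 0.7. The sample size arithmetic is not at fault; it fits the abstract's version, with quality of life as the basis.

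**What to change.** 1. Amend the Study design section to agree with the abstract and the sample size basis, so that SF-12 is the only primary outcome.
2. Name the physical or the mental score as primary, or test both with Holm.
3. State how error is controlled over the three DS-EW contrasts on that outcome. A pre-stated order would do, and which order is the investigators' choice. An omnibus condition-by-time test first is another route, but with four arms the contrasts after it still need an order or an adjustment, because the omnibus step protects fully only when no arm differs. If both scores are kept with ordered contrasts, start each score's sequence at 0.025 and release the full 0.05 to the other only when a whole sequence has succeeded.
4. Report depression, anxiety, growth and medical visits as secondary, without confirmatory claims.

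If an unseen analysis plan already contains steps 2 and 3, a sentence pointing to it is enough.

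The cost is wording plus some power: about 66% for a pairwise contrast at 0.05 against about 56% at 0.025, assuming d = 0.8. Naming one score and ordering the contrasts keeps the full 0.05 for the first test. The later contrasts can then be claimed only if those before them succeed.

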**Discussion:**

The WRITTEN-HEART study aims to explore and expand the frontiers of the expressive writing research enterprise by investigating the feasibility, safety and clinical efficacy of brief and cost-effective expressive writing interventions in patients with CHD referred to CR.

**Trial registration:**

ClinicalTrials.gov NCT01253486

## Background

The World Health Organization (WHO)'s statistics suggest that cardiovascular diseases (CVDs) are the number one cause of mortality for all males and females, accounting for almost 30% of all global deaths [1].

Despite this alarming scenario, the age-adjusted cardiovascular (CV) death rates have decreased almost 50% during the past 25 years [2]. Improved management of acute myocardial infarction (MI), earlier diagnostic procedures, advanced intervention techniques and especially the recognition and management of CV risk factors have resulted in an increasing number of CVD survivors [3]. However, such gains in survival rates have resulted in a significant increase in physical disability, impaired health-related quality of life and high psychosocial distress, particularly in the rapidly growing population of elderly persons [4,5].

Psychosocial and affective disorders are highly prevalent within cardiac populations and contribute significantly to impair health-related quality of life and also to enhance the prognostic risk for adverse CV events [5]. For example, the prevalence rate of major depression disorder in the National Comorbidity Survey [6] was approximately 5%, compared with a prevalence of 15% or greater in populations with CVD [7]. In addition, at least another 15% to 20% of patients with cardiac disease exhibit depressive symptoms that do not necessarily meet criteria for major depressive disorder [7]. Similarly, anxiety disorders, such as phobic anxiety or panic disorder, are relatively common among patients with CVD. As a consequence, cardiologists are likely to encounter a significant number of psychologically distressed patients in medical practice [5]. Clinical health psychologists have thus an important role in helping to develop effective psychosocial interventions for this population [8,9].

### Study rationale

A number of controlled experiments have demonstrated the physical and psychosocial benefits of expressive writing. Developed by Pennebaker and Beall [10], the procedure typically involves random assignment of individuals to one of two conditions, with instructions to write about their deepest thoughts and feelings regarding a stressful experience or about innocuous topics (control) over several brief writing sessions.

A recent special issue of the British Journal of Health Psychology edited by Joshua Smyth and James Pennebaker [11] confirms the breath of current interest in the expressive writing paradigm and invites to look forward at the many remaining frontiers in Expressive Writing research. One of the boundary conditions that have been identified in their commentary paper concerns new outcome measures and previously unexamined populations. Surprisingly, the expressive writing procedure has never been used with patients with CVD. Perhaps, clinical researchers have been negatively impressed by some negative results [12]. Furthermore, in a review on the putative theories underlying the expressive writing procedure, Sloan and Marx concluded that it was too early to say definitively whether expressive writing is a trustworthy technique that should be adopted by the therapeutic community [13]. However, the meta-analysis by Frisina, Borod and Lepore [14] on 9 writings studies using clinical populations showed that expressive writing significantly improved health outcomes (d = .19) and the strongest effect was found for physical health outcomes (d = .21). Moreover, the expressive writing procedure is tremendously cost-effective, easy to administrate, feasible and brief, does not need highly trained clinicians to work, has a great accessibility and has shown an amount of promising objective and subjective health benefits in many studies on college students and individuals from the community. Such appealing features have made it very attractive for some clinicians and clinical researchers who, beginning in the 90s and going on until nowadays, have started to use the expressive writing procedure with their patients and to examine its effects empirically in many randomized clinical trials involving individuals with physical disorders such as breast cancer [15-18], rheumatoid arthritis [19], fibromyalgia [20], HIV [21,22], renal cell carcinoma [23], men diagnosed with prostate cancer [24], women with chronic pelvic pain [25], men with elevated blood pressure [26], patients undergoing bladder papilloma resection [27] and transurethral prostate resection [28].

The fact that no trial to date has yet evaluated the effects of expressive writing on patients with CVD is surprising because many studies on the physiological effects of expressive writing have found significant and beneficial variations in many markers of the autonomic nervous system such as skin conductance, heart rate, heart rate variability and blood pressure [e.g., [17]]. It is even more disappointing that the small but significant study of McGuire, Greenberg and Gevirtz [26] on the autonomic effects of expressive writing in individuals with elevated blood pressure has been neither replicated nor expanded in the subsequent years. In their paper, McGuire, Greenberg and Gevirtz argued that, given the high costs and potential risks of elevated blood pressure and the lack of demonstrated effective non-pharmacological treatments for this population, a low-cost and easily administered psychological intervention as expressive writing, if shown to be effective, has the potential for widespread clinical use. Although they showed that, one month after writing, the participants who were allocated in the expressive writing condition exhibited lower systolic and diastolic blood pressure than before writing and that, four months after writing, diastolic blood pressure remained lower than baseline levels, their argument felt on deaf ears. As elevated blood pressure is a major neuro-cardiovascular risk factor that often affects patients with an established CVD, an intriguing idea is to administer the expressive writing procedure to a sample of patients with CVD referred to cardiac rehabilitation (CR) and test the brief, mid and long-term effects of such an intervention on patients' health-related quality of life (HRQoL), anxiety symptoms, depressive symptoms, medical consultations for cardiovascular morbidity and post-traumatic growth. With respect to the latter outcomes, same evidence suggests that expressive writing is effective in enhancing positive growth from trauma over time [29] and a body of research has shown that awareness of the benefits of adverse events and circumstances is an important predictor of successful adjustment [30-32].

Further empirical support to the rationale of this study comes from the results of a recent clinical trial on potential physiological, emotional and cognitive mechanisms underlying the positive health effects produced by disease-related expressive writing in a sample of women with early stage breast cancers [17]. Findings supported the hypothesis that autonomic activity (heart rate) mediates the effect of the expressive writing condition on self-reported physical symptoms. Findings suggested that the prolonged and repeated exposure and concomitant cognitive processing might contribute to improved regulation of physiological responses, presumably leading to less stress on bodily systems and ultimately enhanced physical health [17].

A second goal of the study is to determine whether the effects of the expressive writing intervention vary as a function of four potential moderating variables: coping styles, negative affectivity and social constraint (type D personality factors), perceived social support and evaluative ratings of the writing intervention. In fact, some evidence suggests that expressive writing may be most effective for individuals who use more approach-oriented, expressive coping strategies than for those who are more non-expressive or have deficits in identifying and processing emotion [33-35]. Further, same evidence suggests that perceived emotional support is a moderator of the expressive writing effects. This hypothesis was guided by social constraint theory, which suggests that the absence of social outlets for emotional expression and processing has a negative effect on adjustment to stressful situations and that expressive writing may represent a useful intervention for individuals who lack opportunities for emotional expression in their social environments [36].

